#### Staged Revascularization

Staged PCI will be performed 4 weeks after the first PCI performed in the setting of the ACS. PCI will be performed with newer-generation drug eluting stents at the operator's discretion. Use of intracoronary imaging is allowed, but not for the assessment of the relevance of the stenosis (i.e., not for overruling the decision made by angiography or QFR). FFR or other invasive hemodynamic assessments prior to PCI are not allowed.

Reference vessel diameters calculated by the QFR software will be used.

#### SAQ Questionnaires

The first SAQ questionnaire will be administered before the staged revascularization, i.e., ~4 weeks after the ACS event. The SAQ-7 provides a quantitative analysis of 5 domains (physical limitation, angina stability, frequency, treatment satisfaction, and quality of life) reflecting the impact of angina on patients' health status during the previous 4 weeks. Scores for each domain go from 0 to 100, with 100 defining absence of limitations. The SAQ score at 1 month after ACS correlates with the subsequent incidence of mortality, hospitalization, and resource use (22). The SAQ-7, along with clinical follow-up data (death, re-hospitalization, re-intervention) will be collected at 3 and 12 months after protocol-mandated complete revascularization during office or telephone visits.

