### Study Endpoints

*Primary endpoint (functional): the primary endpoint (functional) is* the proportion of patients assigned to medical treatment in the two groups (QFR vs. Reference) (see Table 2).

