### Power Calculation

Functional endpoint: For the sample size calculation, the results of the FLOWER-MI trial will be used. In this study, which enrolled multivessel disease patients with at least one non-culprit lesion >50%, PCI was performed in 388 of 586 patients (66.2%) in the FFR-guided group and in 560 of 577 patients (97.1%) in the angiography-guided group; 366 of 826 (44.3%) lesions in the FFR group were reclassified from angiographically significant to non-significant based on FFR. Of note, although we allow patients with lesions >30% in our study, we foresee that [based on the results of the FLOWER-MI (10)], about 97% of the participants in our study will have at least one lesion >50%. Conservatively, we hypothesize a rate of decision to not perform PCI in our angiography group 4 times higher than that observed in the FLOWER-MI study (i.e., 13%). In the QFR group, we hypothesize a conservative decision in 33% (similar to that observed in the FLOWER-MI study). Based on this hypothesis, 176 patients are required to have a 90% chance of detecting, as significant at the 5% level, a decrease in the primary outcome measure from 33% in the QFR group to 13% in the angiography group.

Clinical endpoint: The clinical endpoint combines hard endpoints and angina: in the FORZA trial, comparing a FFR-guided with a OCT-guided PCI strategy, a composite of MACE + significant angina (all-cause death, non-fatal myocardial infarction, target vessel revascularization, SAQ <90) was taken. The incidence of this endpoint was 14.8% at 1 year in the FFR group (23). The incidence of the same endpoint in the FAME trial was 32.4% at 1 year in the angiography group (3). Given these assumptions, 176 patients are required for a power of 80% and an alpha error of 5% to observe a difference assuming an incidence of 14.8% in the QFR group and 32.4% in the angiography group.

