### Statistical Analysis of Primary and Secondary Endpoints

Data will be presented as counts (percentages) and mean ± SEM as appropriate and will be analyzed using parametric or non-parametric tests. The primary functional endpoint will be assessed as difference in proportions and the relative risk between groups will be estimated with exact 95% confidence intervals and *P*-values. The proportion of patients with primary functional clinical endpoint and other binary outcomes will be analyzed using the same methods, and time to events within 12 months will be compared between groups using log-rank tests. A multivariable stepwise linear regression (*p* < 0.2 to enter, *p* < 0.1 to stay) analysis will be used. Covariates will include age, sex, diabetes, smoking, renal function, previous myocardial infarction, type of acute coronary syndrome presentation, body mass index, vessel(s) involved. The grouping factor (QFR vs. angiography) will be forced into the model. A *p*-value <0.05 (2-sided) will be considered statistically significant. All secondary endpoints will be analyzed by descriptive statistics and appropriate exploratory *p*-values.

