Our study has several limitations. First, the study population is relatively small and the study is not designed to test hard clinical endpoints. Second, the presence of diffuse spasm at the time of an ACS might lead to an overestimation of non-culprit lesions in both groups. In a recent study by Sejr-Hansen et al., QFR performed in the setting of a ACS showed however a very good correlation with staged QFR and also a good diagnostic performance as compared to staged FFR (38). Based on these data, QFR performed in the acute setting appears to maintain its clinical validity. Third, the primary endpoint is assessed at 12 months after protocol-mandated complete revascularization; complaints due to myocardial ischemia, which may occur after a period of more than 1 year, will not be recorded. However, data from the ischemia trial appear to suggest that the incidence of angina remains constant during longer follow-up periods (39).

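### Follow-up and the clinical endpoint are dated from a staged revascularization that an expected 33% of QFR and 13% of angiography patients will not have, and the visible text gives no common time origin

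*Protocol article*

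**What the plan says.** The SAQ Questionnaires section states that the SAQ-7 and the clinical follow-up data "will be collected at 3 and 12 months after protocol-mandated complete revascularization during office or telephone visits". The limitations paragraph of the Discussion says that "the primary endpoint is assessed at 12 months after protocol-mandated complete revascularization".

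Under Consent and Randomization, patients are randomized after the culprit lesions have been treated, and the non-culprit lesions selected by either strategy are then treated in one staged session. The Staged Revascularization section gives its timing: "Staged PCI will be performed 4 weeks after the first PCI performed in the setting of the ACS". The first SAQ is taken at about the same time, before that session.

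Not every patient has the session. The share assigned to medical treatment is the primary functional endpoint, and the Power Calculation plans for "a decrease in the primary outcome measure from 33% in the QFR group to 13% in the angiography group".

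Elsewhere the time origin is left open. Study Endpoints places the clinical composite at 12 months without saying from when. The analysis section says that "time to events within 12 months will be compared between groups using log-rank tests", again without a start. Safety Analyses has clinical data collected at hospital discharge and at the 3- and 12-month contacts.

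**The concern.** A start date that applies to both arms must exist for every randomized patient and must not depend on what happens after randomization. This one fails on both counts. It is a treatment step whose occurrence is decided by the strategies being compared, and its absence is itself the functional endpoint. The rule as written therefore cannot be applied to patients assigned to medical treatment, and the two arms contain different shares of such patients.

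Four things are left unsettled:

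- **Time zero for medically assigned patients.** Dating them from the index PCI and the others from staged PCI would place the windows about 4 weeks apart.
- **Events between randomization and staged PCI.** They are apparently collected, but the text does not say that they count. A patient who dies while waiting never reaches the stated start.
- **The origin of the log-rank tests.**
- **The date of the 12-month visit for these patients.** It matters beyond scheduling, because the primary (modified intention-to-treat) population is restricted to patients with a 12-month assessment.

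**Working it through.** **1. Inputs.** From the Power Calculation: medical treatment in 33% (QFR) and 13% (angiography); clinical composite in 14.8% and 32.4% at 1 year. From the Hypothesis section: 100 patients per group. From Staged Revascularization: an interval of 4 weeks (28 days).

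**2. The plan's own figure.** With the unpooled two-proportion formula, two-sided 5% alpha and 1:1 allocation,

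n per arm = (z_alpha/2 + z_power)² × [p1(1−p1) + p2(1−p2)] / (p1−p2)²

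- Functional endpoint, 90% power: (1.960 + 1.282)² × (0.2211 + 0.1131) / 0.20² = 87.8, so 88 per arm and 176 in total.
- Clinical endpoint, 80% power: (1.960 + 0.842)² × (0.1261 + 0.2190) / 0.176² = 87.4, so 88 per arm and 176 in total.

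Both stated totals of 176 reproduce. The time origin is not an input, so the sample size does not change.

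**3. Patients without the anchor event.** 0.33 × 100 = 33 and 0.13 × 100 = 13. Together that is 46 of 200 (23%), with a 20-point difference between arms. Staged PCI is expected in 67% and 87%.

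**4. Windows of unequal length (illustration).** Assume a constant hazard, no treatment effect, and a 12-month risk between 14.8% and 32.4%. Lengthen the window by 28 days for medically assigned patients only:

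- Risk 14.8% becomes 15.84%. Arm difference = 0.20 × 1.04 = 0.2 points.
- Risk 32.4% becomes 34.40%. Arm difference = 0.20 × 2.00 = 0.4 points.

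Shortening it by 28 days gives 13.75% and 30.34%, which is the same size of difference (0.2 to 0.4 points) in the other direction.

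**5. First 4 weeks counted only for medically assigned patients.** The hazard soon after an acute coronary syndrome may well exceed the average, so step 4 may understate this case. The documents give no 4-week risk. Assuming 2% to 10%, the spurious difference is 0.20 × 2% = 0.4 points to 0.20 × 10% = 2.0 points.

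**6. Staged-procedure infarctions left out.** The documents give no rate. Assuming 5% to 10% of staged PCIs:

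| | QFR (67% staged PCI) | Angiography (87% staged PCI) | Net between arms |
|---|---|---|---|
| 5% | 3.4 points | 4.4 points | 1.0 point |
| 10% | 6.7 points | 8.7 points | 2.0 points |

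The bias in the comparison is the last column. More events would be lost from the angiography arm, so this omission would work against showing QFR superiority.

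**7. Yardstick.** The design difference is 32.4 − 14.8 = 17.6 points.

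**The case against.** The strongest reply is that the two sentences fix when data are collected and when the endpoint is assessed, not when event counting begins. Safety Analyses collects clinical data from discharge. The primary composite names type 4 infarction, the secondary composite names peri-procedural infarction, and periprocedural biomarker release is defined within 48 hours of the procedure. A reader might infer that early events and staged-procedure infarctions are excluded. The documents do not say so, and naming these infarctions as components points the other way. This part of the reply stands.

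A reader might also take the per-arm losses in step 6 (about 3 to 9 points) as the size of the bias. They are not: the comparison is affected only by the net 1 to 2 points, and only on an assumed rate.

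Two benign readings exist. A patient with nothing further to treat might count as completely revascularized at the index PCI, or the first SAQ at about 4 weeks might be the common start. Both are possible, but neither is stated. They put time zero about 4 weeks apart, and the first gives different calendar windows to shares of patients that differ by arm.

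The primary analyses compare proportions, and the log-rank test is additional. The functional endpoint has no clock. This limits the consequence but does not remove it, because the clinical composite still needs a 12-month date.

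Finally, this is a condensed article, and Figure 1 and Table 2 are not shown. Visit windows may be set out there or in a fuller document. Missing detail alone would be no finding. Here, however, the article states the anchor twice, and the stated anchor cannot be applied to every randomized patient.

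**Conclusion.** The point holds as a defect in a stated rule and should be fixed. Follow-up and the primary clinical endpoint are dated from a strategy-dependent event after randomization that, on the plan's assumptions, 46 of 200 patients lack, in shares differing by 20 points between arms. The visible text supplies no common origin for these patients or for the log-rank tests, and does not settle whether events before staged PCI count.

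The numerical effect on the 12-month composite is probably modest: 0.2 to 0.4 points from windows of unequal length, 0.4 to 2.0 points if early events count only in medically assigned patients, and a net 1 to 2 points if staged-procedure infarctions were dropped, against 17.6 points. These figures rest on the planned 33% and 13%. The first also needs a constant hazard with no treatment effect, and the other two rest on assumed risks that the documents do not give. They do not support a conclusion that the randomized comparison is invalid or that the planned effect could be an artefact of the clock. The reason to act is that a choice of origin made once data are in hand would be open to challenge.

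**What to change.** Amend the SAQ Questionnaires section, the analysis section and the limitations paragraph of the Discussion as follows:

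- Time zero is the date of randomization for every patient and every clinical event, including the log-rank tests.
- All events count from then, including those before and during staged PCI, to the same fixed day in both arms. About 13 months after randomization would keep 12 months beyond the 4-week point.
- The 3- and 12-month SAQ visits are scheduled from one calendar anchor that every patient has, whether or not staged PCI is done. A fixed interval after the index PCI that matches the first SAQ at about 4 weeks would serve. The 12-month assessment that defines the primary population uses the same anchor.

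No treatment and no procedure timing changes. The cost is wording, re-dating of events already recorded, and small visit-window shifts for some patients. Recruitment began in October 2020, so the amendment should be dated and made before any comparison by arm.

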### Study Endpoints

*Primary endpoint (functional): the primary endpoint (functional) is* the proportion of patients assigned to medical treatment in the two groups (QFR vs. Reference) (see Table 2).

**Table 2 T2:**
[figure not shown]
Study endpoints.

*Primary endpoint (clinical):* the primary endpoint (clinical) is a composite of patient-oriented events and significant angina (all-cause death, non-fatal myocardial infarction including type 1, 2, 4, unplanned hospitalization for angina or heart failure, unplanned revascularization, SAQ <90) at 12 months.

*Secondary endpoints:* the secondary endpoints include the following (at 3 and 12 months):

– the percentage of discordant results between functional (QFR ≤ 0.80) and angiographic coronary stenosis severity (diameter stenosis >70%).– the change in severity of angina pectoris as assessed by the SAQ summary score.– changes in the SAQ-7 domains (SAQ Physical limitation scale; SAQ angina stability scale; SAQ angina frequency scale; SAQ quality of life; SAQ Treatment Satisfaction).– incidence of a patient-oriented composite endpoint and its components (cardiovascular death, non-fatal myocardial infarction including peri-procedural, unplanned revascularization, unplanned hospitalization for angina, SAQ summary score <90) and its individual components.

### Sensitivity Analysis

A sensitivity analysis will test the primary and all secondary endpoints in patients with intermediate stenoses >50% (i.e., patients with intermediate non-culprit lesions 30–50% will be excluded from this analysis).

### Adjudication of Events

All clinical events will be adjudicated by a clinical events committee composed by members who are blinded to the allocation group.

### Recruitment

Patient recruitment is performed within the patients treated at the Department of Cardiology, Cardiology 1 of the University Medical Center Mainz.

### Statistics

Statistical analysis will be performed with the MedCalc Software (Ostend, Belgium) and SPSS version 24 (SPSS, Chicago, Illinois).

All subjects who signed informed consent and are assigned a randomization number are considered as ITT subjects, even if they have not received trial treatment. All randomized subjects who were randomized and have a 12-month assessment of the primary endpoint variable will be included in the modified Intention-to-treat (mITT) population. This population is the primary analysis population. Within the mITT population subjects will be assigned to the treatment to which they were randomized. Missing values of SAQ-7 will not be replaced or imputed for the primary analysis.

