### Study Procedures

#### Consent and Randomization

Patients will be contacted after successful interventional treatment of the ACS, which includes treatment of all culprit lesions (typically >90% diameter stenosis or thrombotic lesions) and guideline-directed medical therapy. If all inclusion and no exclusion criteria are met, consent will be obtained. Prior to randomization, QFR will be measured in all participants in all coronary arteries presenting a lesion with 30–90% diameter stenosis. Patients with vessels with residual QFR <0.80 (residual QFR is the QFR calculated in the absence of the target lesion. A QFR <0.80 assumes that treatment of this/these focal lesion(s) would not remove the source of ischemia, such as in the case of diffuse disease) will be excluded. Thereafter, randomization will be performed in a 1:1 ratio with the use of randomly permuted blocks of 2, 4 or 6. The participants and treating physicians will be blinded to the treatment group allocation. Patients will be randomized to one of two strategies: angiography-guided (reference) or QFR-guided revascularization (experimental). In the reference arm, any decision regarding the treatment of non-culprit lesions will be based on the angiography performed at the time of the index PCI and the physicians will be kept blinded to the outcomes of QFR analysis. This strategy reflects the typical procedures used in daily routine; all lesions believed to be significant at angiography will be treated in one staged session. In patients randomized to QFR-guided revascularization, all lesions (one or more per vessel) associated with a vessel QFR <0.80 and a residual QFR >0.80 will be treated in one staged session (13). The treatment plan will be scheduled (according to angiography or QFR) by study investigators not involved in patient care. Only experienced medical staff, certified to use the software with the QFR system, will perform the measurements. Analyses will be conducted with QAngio XA 3D from Medis Medical Imaging Systems BV (Leiden, the Netherlands).

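### The primary analysis population is limited to patients with a 12-month assessment, which drops classifiable patients from the functional endpoint and known non-fatal events from the clinical composite

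*Protocol article*

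**What the plan says.** The Statistics section defines two populations. The first is the full randomised set: "All subjects who signed informed consent and are assigned a randomization number are considered as ITT subjects". The second consists of randomised patients who "have a 12-month assessment of the primary endpoint variable will be included in the modified Intention-to-treat (mITT) population". Of the second it says "This population is the primary analysis population", with patients kept in the arm to which they were randomised. The ITT set is given no analysis. The section adds: "Missing values of SAQ-7 will not be replaced or imputed for the primary analysis".

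The protocol has two primary endpoints, and the population rule makes no distinction between them.

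- **Functional** (Study Endpoints): "the proportion of patients assigned to medical treatment in the two groups (QFR vs. Reference". Under Consent and Randomization, "Prior to randomization, QFR will be measured in all participants in all coronary arteries presenting a lesion with 30–90% diameter stenosis", and "The treatment plan will be scheduled (according to angiography or QFR) by study investigators not involved in patient care". Staged PCI follows 4 weeks after the first PCI (Staged Revascularization).
- **Clinical** (Study Endpoints): a composite of all-cause death, non-fatal myocardial infarction, "unplanned hospitalization for angina or heart failure, unplanned revascularization, SAQ <90) at 12 months". Follow-up is by office or telephone visit at 3 and 12 months (SAQ Questionnaires).

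Under Safety Analyses, the definition of death states that every death enters the comparison in the primary analysis.

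**The concern.** A population conditioned on a 12-month assessment is defined by something that happens after randomisation. The comparison is then protected by randomisation only if having that assessment is unrelated to outcome and to arm. That is doubtful here. Patients with angina or a recent event may differ in how readily they are followed. Participants are blinded to allocation, but whether they had a staged PCI is evident to them, and the plan expects its frequency to differ between arms.

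The two endpoints suffer differently. For the functional endpoint the restriction serves no purpose, since the classification exists long before month 12. For the clinical composite it can discard patients whose endpoint status is already established. Both primary results of a superiority trial are affected.

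**Working it through.** **1. The plan's own figure.** Power Calculation gives 176 patients for each primary endpoint. With two-sided 5%, 1:1 allocation and unpooled variance,

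n per arm = (z₁₋α/₂ + z₁₋β)² × [p₁(1−p₁) + p₂(1−p₂)] / (p₁−p₂)².

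- Functional, 33% vs 13%, 90% power: (1.960 + 1.282)² × (0.2211 + 0.1131) / 0.20² = 87.8, so 88 per arm, 176 in total.
- Clinical, 14.8% vs 32.4%, 80% power: (1.960 + 0.842)² × (0.1261 + 0.2190) / 0.176² = 87.4, so 88 per arm, 176 in total.

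Both figures reproduce. The planned recruitment is 100 per group (Hypothesis section). No loss rate is stated, so every loss rate below is an assumption.

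**2. Functional endpoint: what the restriction costs.** Power for 33% vs 13%, two-sided 5%, with the pooled-variance test (slightly stricter than the plan's formula: 89.0% at N=176):

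| Assumed loss | N analysed | Power |
|---|---|---|
| none (all randomised) | 200 | 92.5% |
| 5% | 190 | 91.2% |
| 10% | 180 | 89.7% |
| 20% | 160 | 85.9% |

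Loss that depends on treatment assignment also shifts the estimate. With fraction m_med of medically assigned and m_PCI of PCI-assigned patients lost, the observed proportion is p(1−m_med) / [p(1−m_med) + (1−p)(1−m_PCI)].

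- m_med = 15%, m_PCI = 5%: QFR 0.2805/0.9170 = 30.6%, angiography 0.1105/0.9370 = 11.8%. The difference is 18.8 points instead of 20, and power is 88.6%.
- The reverse (5% and 15%): 35.5% vs 14.3%, a difference of 21.2 points.

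The effect is modest in either direction, but all of it is avoidable.

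**3. Clinical composite: which patients the rule removes.**

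| Patient | Endpoint known? | In the mITT set? |
|---|---|---|
| Non-fatal component event, then lost before month 12 | Yes, an event | No |
| Death before month 12 | Yes, an event | Unclear: Statistics does not secure it, Safety Analyses implies it |
| No event, no 12-month SAQ | No | No |
| 12-month assessment obtained | Yes | Yes |

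Only the third row is truly missing.

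**4. Clinical composite: how far the result could move.** Take the planning rates as the complete-case rates and assume 10% loss in each arm.

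- QFR over all randomised: 0.9 × 14.8 = 13.3% if no missing patient has an event; 13.3 + 10 = 23.3% if all do.
- Angiography: 0.9 × 32.4 = 29.2% to 39.2%.
- Extremes of the difference (QFR minus angiography): 23.3 − 29.2 = −5.8 and 13.3 − 39.2 = −25.8 points (from unrounded rates), around a complete-case value of −17.6.

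A less extreme case: a true rate of 25% in both arms, with 20% of event patients missing in one arm and 5% of everyone else. The first arm then shows 0.25×0.80 / (0.25×0.80 + 0.75×0.95) = 0.2000/0.9125 = 21.9%, the other 25.0%. The 3.1-point difference is due to the population rule alone.

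**The case against.** The strongest counter-argument concerns deaths. A reader might infer that anyone who dies before month 12 is removed, so that an arm with more deaths could look better. The documents do not support stating that as fact. The rule asks for an assessment of the primary endpoint variable, not of the SAQ, and for a patient who has died the composite is already determined. Safety Analyses places all deaths in the primary analysis, although that sentence may mainly mean all-cause rather than cardiac death. What stands is that two sections need reconciling. Even if deaths were dropped, the effect would depend on their balance: with an assumed 3% in each arm, 14.8% and 32.4% become 12.2% and 30.3%, a difference of 18.1 instead of 17.6 points.

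A reader might also say that the rule selects on the outcome. It selects on whether the outcome is available, not on its value. Nor does the surplus of 200 recruited over the 178 in the Hypothesis section show a planned loss rate: 178 belongs to the 3-month SAQ summary score hypothesis, and no dropout allowance is given there.

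Three further points have some force. Telephone follow-up should keep losses low. Adjudication of all clinical events and the planned log-rank tests suggest that early events were meant to count, but neither overrides the population rule. Missing-data sensitivity analyses are commonly left to an SAP, so their absence is not held against the article; the point rests on what the Statistics section affirmatively fixes.

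For the functional endpoint one could argue that a 12-month assessment of its variable has no meaning, so the restriction cannot apply. Yet only one primary population is named, and the text would need correcting on that reading too.

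**Conclusion.** The point holds in this form. As written, the sole primary population depends on follow-up after randomisation. It drops patients who can be classified for the functional endpoint, and it drops patients with a documented non-fatal component event who are later lost. The status of deaths before 12 months is ambiguous between two sections; the documents do not establish that deaths are excluded.

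The cost to the functional endpoint is small: about 3 points of power at an assumed 10% loss. For the clinical composite the consequence is potential bias whose direction cannot be predicted. It arises only where availability of the assessment is related to outcome or arm. The range in step 4 is a worst-case bound under an assumed loss, not an expected shift.

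**What to change.** Before the data are analysed, change the Statistics section as follows.

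- **Functional endpoint:** analyse all randomised patients as randomised, with no reference to a 12-month visit.
- **Clinical composite:** make ITT the primary population. Count any documented component event up to 12 months, including death, whether or not a 12-month SAQ exists. Align this wording with the statement on deaths under Safety Analyses.
- **Missing data:** treat only event-free patients without a 12-month SAQ as missing, and replace the no-imputation sentence with a stated method. Multiple imputation using arm and the baseline and 3-month SAQ is one suitable option among several. Add best-case and worst-case sensitivity analyses.
- **mITT:** keep the present definition as a supportive analysis.

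The cost is a change of wording and one missing-data analysis. No additional data are needed, because event reports and the earlier SAQ scores are already collected.
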